### Endpoints

2.4

The primary endpoint is the change of cardiac function [LV end-systolic volume index (LVESVi)] measured by cardiac magnetic resonance (CMR) in T2DM patients with AMI. The secondary endpoints are (I) other changes in parameters of cardiac function measured by CMR and echocardiography (LVEF, LV mass, LV volume); (II) change in KCCQ-OS and EQ-5D from baseline; (III) change in biomarkers related to myocardial parietal stress [N-terminal fragment brain natriuretic peptide (NT-pro BNP)], myocyte injury (creatine kinase, TnI, TnT), fibrosis (sST2, Gal-3), inflammation including interleukin-1β (IL-1β), interleukin-6 (IL-6), interleukin-8 (IL-8), interleukin-10 (IL-10), tumor necrosis factor-α (TNF-α), procalcitonin (PCT), C-reactive protein (CRP), and FGF21 in hospital laboratory research, as well as miRNA level. The detailed endpoints are provided in **Table 2**.

**Table 2 T2:** Trial endpoints.

	Outcome measures
Primary endpoint	
Cardiac function in T2DM patient with AMI 12 months after the event	Change in LVESVi from baseline to the study end at 12 months measured by cardiac MRI
Secondary endpoints	
1. Parameters of cardiac structure	Change in LVEF, LV mass, LV volume at 3 months, 6 months, and 12 months after hospitalization for new-onset AMI
2. Biomarkers related to myocardial parietal stress 3. Biomarkers related to AMI 4. Biomarkers related to fibrosis 5. Biomarkers related to inflammation	Change in NT-pro BNP; Change in CK, TnI, TnT; Change in sST2, Gal-3; Change in IL-1β, IL-6, IL-8, IL-10, TNF-α, CRP, and PCT; at 3 months, 6 months, and 12 months after hospitalization for new-onset AMI
6. Questionnaire’s instructions on health status	Change in KCCQ-OS and EQ-5D at 3 months, 6 months, and 12 months after hospitalization for new-onset AMI
Exploratory endpoints on the mechanisms	
To investigate that whether SGLT2i will have an effect on miRNAs and FGF21	Change in miRNAs and FGF21

AMI, acute myocardial infarction; LVESVi, LV end-systolic volume index; MRI, magnetic resonance imaging; eGFR, estimated glomerular filtration rate; SGLT2i, sodium-glucose cotransporter-2 inhibitor; LV, left ventricular; EF, ejection fraction; NT-pro BNP, N-terminal fragment brain natriuretic peptides; CK, creatine kinase; TnI, Troponin I; TnT, Troponin T; sST2, soluble suppression of tumorigenicity-2; Gal-3, galectin-3; KCCQ-OS, Kansas City Cardiomyopathy Questionnaire overall summary score; EQ-5D, EuroQol- 5 dimension; FGF21, fibroblast growth factor 21.

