#### Blood samples

2.7.1

Blood samples for routine biomarkers (NT-pro BNP, creatine kinase, TnI, TnT, sST2, IL-1β, IL-6, IL-8, IL-10, TNF-α, CRP, PCT, Gal-3) will be collected and measured by the hospital laboratory service from the eligible patients within 14 days after AMI incidence and at 1-year follow-up. A total of approximately 8 mL of blood samples will be drawn from the antecubital vein into two vacuum blood collection tubes at two time points: on the first 14 days of AMI (admission) and at 1 year following AMI. To obtain plasma, 4 mL of blood sample with anticoagulants (EDTA) will be centrifuged at 3,000 rpm for 10 min at 4°C, then the yellow cell-free supernatant will be collected and frozen in RNase-free Cryo-Tubes under -80°C until further processing. To obtain serum, the tubes without anticoagulants within 4 mL of peripheral blood samples are let stand at a 45- to 60-degree angle under 4°C for at least 1 h to promote coagulation. Then, the blood is centrifuged within 10 min of withdrawal at 3,000 rpm for 10 min to obtain the serum, which will be separated into RNase-free tubes. The handled samples are stored under -80°C to be used further for the miRNAs and FGF21 detector.

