#### Statistical analysis

2.8.2

Continuous variables will be described as mean with SD and compared by unpaired Student’s t-tests or Mann–Whitney U tests. Categorical variables of baseline characteristics will be summarized using count statistics, presented as percentage n (%) as appropriate. Chi-square test will be used when sample size is larger than 40; Fisher’s exact test will be used when sample size is smaller than 40. The results with p values <0.1 in univariate regression or considered meaningful in clinical practice will be further analyzed using multivariate regression to explore the effects of SGLT2i on LV function. All analyses will be conducted using the SPSS software, version 22.0 (SPSS Inc., Chicago, IL, USA).

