The target population in this study are patients with T2DM and AMI. A large cohort study (n = 2,596) manifested that almost 70% of AMI participants developed HF within 7.6 years, which was associated with LV remodeling (37, 38). Thus, early intervention to prevent LV remodeling and post-AMI heart failure is crucial. Due to a growing body of evidence on SGLT2i in a CVD population (19), it is reasonable to investigate whether early initiation of SGLT2i in patients with AMI improves cardiovascular outcomes. In the EMPA-REG OUTCOME trial, empagliflozin decreased cardiovascular mortality and HF hospitalization in patients with T2DM and a history of MI (3). At present, eight clinical investigations related to SGLT2i have been conducted in AMI patients with DM (9, 39, 40). Notably, three studies, specifically the EMMY study (41), SGLT2-I AMI PROTECT (39, 40), and EMBODY (42) study, have effectively disseminated their findings. The EMMY study revealed that the changes in LVESV and LVEDV were lower by 7.5 mL (p = 0.0003) and 9.7 mL (p = 0.0015), respectively, in the empagliflozin group compared to the placebo group, and a significant reduction in NT-pro BNP levels was observed in the empagliflozin group (41). An observational registry SGLT2-I AMI PROTECT exhibited that those receiving SGLT2-I can significantly reduce inflammatory response and infarct size compared to those receiving other oral antidiabetic agents, and the use of SGLT2-I showed a lower risk of adverse cardiovascular outcomes (39, 40). The EMBODY study demonstrated that early SGLT2i administration might be effective in improving cardiac nerve activity without any adverse events (42). So far, the remaining five studies (EMPACT-MI, EMPRESS MI, DAPA-MI, NCT03658031, and NCT03591991) have not yet been published (9, 43). These studies did not explore the cellular-level mechanisms throughout their investigations, while our research endeavors to study the impact of SGLT2i on the structural aspects of the cardiac domain within the Asian population. To achieve this, we employ magnetic resonance imaging and blood work on its potential mechanisms underlying the favorable action on cardioprotection function. Additionally, such high-risk population with diabetes and AMI are commonly paid more attention on improvement in quality of life (14). A recent prospective study has provided compelling evidence suggesting the beneficial effect of empagliflozin on cognitive and physical impairment in frail older adults with T2DM and preserved ejection fraction (HFpEF) (44). This finding has sparked our interest in investigating whether the results are similar to those of a population with T2DM and AMI. KCCQ-OS is initially designed for patients with HF to evaluate symptom frequency, physical limitation, quality of life score, and social limitation (33). A recent cohort study included HFrEF patients exhibited that KCCQ-OS is more sensitive in health status over time than New York Heart Association (NYHA) class considering as a cornerstone for quantifying the health status of HF population (34). It is unknown whether KCCQ-OS is applicable to AMI population with high risks of HF. Moreover, we will also use EQ-5D to evaluate the quality of life in terms of five dimensions including mobility, self-care, activities, anxiety/depression, and pain/discomfort (35). Both full scores are ranging from 0 to 100, with higher scores reflecting better health status.

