However, it is important to acknowledge certain limitations of this study. This trial is a parallel group and single-center research that recruits patients with T2DM and severe AMI with complex conditions such as HF or CKD. Thus, whether these findings can speculate to other more uncomplicated patients needs to be further studied. To enhance the credibility of the results, the study employs univariate and multivariate analyses to migrate the possible influences.

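### The covariate rule for the adjusted SGLT2i effect uses univariate p<0.1 or open judgement, neither restricts candidates to pre-treatment variables nor forces the treatment term in, and so permits adjustment for treatment-affected markers

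*Protocol article*

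**What the plan says.** The rule is in section 2.8.2, Statistical analysis: "The results with p values <0.1 in univariate regression or considered meaningful in clinical practice will be further analyzed using multivariate regression". Its declared purpose is "to explore the effects of SGLT2i on LV function". The candidates are called results and are not listed or dated. In that section the word baseline appears only for description: "Categorical variables of baseline characteristics will be summarized using count statistics".

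The Discussion, in the limitations paragraph, gives the model its role: "the study employs univariate and multivariate analyses to migrate the possible influences". The verb is presumably meant as mitigate, so the aim reads as control of confounding.

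Section 2.4, Endpoints, makes marker changes secondary endpoints, beginning with "change in biomarkers related to myocardial parietal stress [N-terminal fragment brain natriuretic peptide (NT-pro BNP". Section 2.7.1 collects the routine biomarkers "from the eligible patients within 14 days after AMI incidence and at 1-year follow-up", so baseline and post-treatment values of each will both exist. Of a cited trial of empagliflozin after AMI the Discussion reports that "a significant reduction in NT-pro BNP levels was observed in the empagliflozin group".

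**The concern.** Section 2.3 allocates by contraindication and prior regimen, not by randomisation. The multivariate model is thus the only confounding-adjusted analysis the article describes. A rule for such a model has to do two things: admit the confounders and keep out the consequences of treatment. This one secures neither.

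- **Consequences of treatment can enter.** A p<0.1 screen selects whatever is associated with LVESVi change, and markers that move with the ventricle over the same year are strong candidates. The article itself expects SGLT2i to act on several of them (NT-proBNP, inflammation, FGF21). Adjusting for one changes the question from the total effect to the part of the effect not shared with that marker.
- **Confounders can fall out.** A variable that differs between groups and predicts LVESVi change can have a univariate p above 0.1 in a sample of this size, especially when its influence runs opposite to the drug effect.
- **The treatment term is not guaranteed.** The sentence never says that SGLT2i group stays in the model whatever its own univariate result.

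At stake is the estimate on which the article rests its credibility. The unadjusted comparison of groups is not touched.

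**Working it through.** **The plan's own figures.** Section 2.8.1 gives changes in LVESVi of -7.9 ± 11.8 and -1.5 ± 11.3 mL/m2, 80% power and α = 0.025. The difference is -7.9 - (-1.5) = -6.4. Reading α as one-sided (equal to 5% two-sided) with SD 11.8 in both groups:

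n per group = 2 × (1.96 + 0.842)² × 11.8² / 6.4² = 53.4, so 54 per group and 108 in all. Then 108 / 0.9 = 120.

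The sample size reproduces and is not in dispute. The checks below use 54 per group and the pooled SD √((11.8² + 11.3²)/2) = 11.55, so SE = 11.55 × √(2/54) = 2.22. Unadjusted power is about 81% at 5% two-sided.

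**Adjusting for one treatment-affected marker.** Assumptions, which the documents do not supply: within groups the marker change correlates r with LVESVi change, and SGLT2i shifts the marker by d SD in the favourable direction.

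Adjusted effect = -6.4 + r × 11.55 × d

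SE = 2.22 × √(1 - r²) × √(1 + d²/4)

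| r | d | Adjusted effect (mL/m2) | SE | Power |
|---|---|---|---|---|
| 0.3 | 0.3 | -6.4 + 1.04 = -5.4 | 2.14 | about 70% |
| 0.5 | 0.5 | -6.4 + 2.89 = -3.5 | 1.98 | about 42% |

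In simulations over this range the marker passed the p<0.1 screen in 97 to 100% of trials, so if it is offered as a candidate it will nearly always be kept.

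A second simulation, set up by the share of the effect that a marker shifted by 0.5 SD carries, agrees:

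| Share carried | Passes screen | Mean adjusted effect (mL/m2) | Power |
|---|---|---|---|
| 0% | 18% | -6.3 | 80% |
| 25% | 96% | -4.8 | 58% |
| 50% | 100% | -3.2 | 38% |

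**Dropping a confounder.** With 108 patients, p<0.1 requires |r| > 1.659 / √(1.659² + 106) = 0.159. Assume, for illustration, a baseline variable that is 0.5 SD higher in the SGLT2i group, has a within-group correlation of 0.15 with LVESVi change, and acts against the drug.

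- Bias if it is left out: 0.15 × 11.55 × 0.5 = 0.87 mL/m2, so the observed difference is -5.53.
- Its univariate covariance with the outcome: 0.15 × 11.55 + 0.25 × 0.5 × (-5.53) = 1.73 - 0.69 = 1.04.
- Its univariate correlation: 1.04 / (√1.0625 × √(11.55² + 0.25 × 5.53²)) = 1.04 / (1.03 × 11.88) = 0.085, about half the threshold.

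In a simulation of this setting it failed the screen in 78% of trials. With a within-group correlation of 0.3 it failed in about 20%. This loss is smaller than the marker problem, but real.

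**The case against.** The strongest reply is that nothing in the article says a follow-up marker will be a covariate. Section 2.4 and Table 2 list these markers as endpoints, the Discussion places the link between miRNAs and CMR under mechanism, and the limitations paragraph uses the language of confounding control. A condensed article may also leave its covariate list to a fuller document. Most of this stands. A reader might infer that change in NT-proBNP will enter and will remove part of the effect; the documents support only that the rule lets it. The missing list is not the complaint. The complaint is the selection rule that is stated, and a fuller document would have to contradict that rule to repair it.

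Two further inferences should be resisted.

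- **A false negative on the primary endpoint.** Section 2.8.2 first compares continuous variables by t-test or Mann–Whitney test. That comparison is unaffected, and the article does not make the adjusted estimate the primary test.
- **Adjustment skipped when the crude SGLT2i result has p≥0.1.** If confounding hid an assumed 3 of the 6.4 mL/m2, crude p<0.1 would occur with probability about 0.45 (3.4 / 2.22 = 1.53, against 1.645). But the clinical-judgement clause would naturally admit the study drug at any p value. The wording leaves this unclear; it does not establish it.

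It is also fair that the correlations and shifts are assumed, and that a marker carrying none of the effect leaves the estimate almost unchanged.

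**Conclusion.** The point holds as a weakness in a stated rule, not as a forecast of what the analysts will do. Univariate p<0.1 or open judgement is a poor way to choose adjustment variables in a comparison whose groups are formed by contraindication. It permits adjustment for treatment-affected markers, it can discard confounders, and it leaves the treatment term's place unstated. If one marker with r and shift of 0.3 to 0.5 were admitted, the adjusted difference would fall from -6.4 to about -5.4 to -3.5 mL/m2, a loss of roughly 16 to 45%. That range rests on assumed inputs and on a marker that SGLT2i moves in the same favourable direction as LV size. The documents allow no firmer figure. The change should be made because it is nearly free and protects the analysis that the Discussion relies on.

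**What to change.** Replace the selection sentence in section 2.8.2 with text to this effect:

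*The SGLT2i group term is kept in every model for LVESVi and the other LV parameters, whatever its univariate p value. Adjustment uses a prespecified set of variables whose values precede the start of study treatment, chosen on clinical grounds and not by univariate p value. Associations of changes in biomarkers, FGF21, miRNA and questionnaire scores with LV change are reported separately as association or mechanism analyses.*

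The set itself should be named before outcome data are examined. Calling a value baseline is not enough to make it pre-treatment. Section 2.3 has SGLT2i prescribed in hospital or continued from an earlier regimen, while sections 2.5 and 2.7.1 allow the first CMR and blood sample up to 14 days after PCI or AMI. The dates of these measurements should therefore be compared with the date of the first study dose.

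The cost is a few sentences. No patients or procedures are added, and the mechanism analyses are all retained. The one downside is that a fixed set may carry a few more covariates than a p<0.1 screen would, in a sample of about 108, so the set should be kept short.

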## Discussion

3

Several studies (3–7) have demonstrated the cardiovascular protective effects of SGLT2i in T2DM patients with high cardiovascular risks. However, inconsistent results on LV functions were shown in clinical trials (22–26) related to specific gliflozin. Thus, in this study, we will concentrate on the influence of SGLT2i on cardiac function.

Limited by a small sample size (only 28 patients per treatment group) and mild severity of HF, the first explorative clinical study (REFORM) failed to observe the effect of dapagliflozin on LVESVi or any other parameter of LV remodeling in participants with symptomatic HF and T2DM (22). Similarly, the EMPA-HEART CardioLink-6 trial showed that empagliflozin had no effect on LVESVi or LV end-diastolic volume index (LVEDVi) in patients with T2DM and coronary artery disease (CAD) (23), with a short follow-up period (only 6 months) and a small portion (8%) of participants having HF. In contrast to the aforementioned studies, SUGAR-DM-HF exhibited that empagliflozin could reduce both LVESVi and LVEDVi in patients with T2DM and reduced ejection fraction (HFrEF) with the mean LVEF (32.5%) for only 9 months (24). The similar positive results were also revealed in EMPA-TROPISM in nondiabetic patients with HFrEF (25). The distinct participant characteristics, disease severity, and sample size are possible explanations for conflicting findings on the relationship between the use of SGLT2i and LV function. Alternatively, we proposed that the background treatment including angiotensin-converting enzyme inhibitor/angiotensin receptor antagonist (empagliflozin vs. dapagliflozin: 82.1% vs. 78.7%) and β-blockers (empagliflozin vs. dapagliflozin: 89.7% vs. 45.0%) was partly attributed to the inconsistent study results (26). We found that the reported improvement of LV function was mainly derived from HF population with lower LVEF or receiving empagliflozin (26).

CMR has emerged as the gold standard for quantifying cardiac function and possess higher reproducibility than echocardiography (36). Recent studies demonstrated that CMR had the potential capability to elucidate the detailed changes in ventricular structure especially in intracellular or extracellular compartments (26, 36). Given that, we performed CMR in addition to echocardiography to acquire more precise images of LV structure, with a specific focus on changes in LVESVi.

The target population in this study are patients with T2DM and AMI. A large cohort study (n = 2,596) manifested that almost 70% of AMI participants developed HF within 7.6 years, which was associated with LV remodeling (37, 38). Thus, early intervention to prevent LV remodeling and post-AMI heart failure is crucial. Due to a growing body of evidence on SGLT2i in a CVD population (19), it is reasonable to investigate whether early initiation of SGLT2i in patients with AMI improves cardiovascular outcomes. In the EMPA-REG OUTCOME trial, empagliflozin decreased cardiovascular mortality and HF hospitalization in patients with T2DM and a history of MI (3). At present, eight clinical investigations related to SGLT2i have been conducted in AMI patients with DM (9, 39, 40). Notably, three studies, specifically the EMMY study (41), SGLT2-I AMI PROTECT (39, 40), and EMBODY (42) study, have effectively disseminated their findings. The EMMY study revealed that the changes in LVESV and LVEDV were lower by 7.5 mL (p = 0.0003) and 9.7 mL (p = 0.0015), respectively, in the empagliflozin group compared to the placebo group, and a significant reduction in NT-pro BNP levels was observed in the empagliflozin group (41). An observational registry SGLT2-I AMI PROTECT exhibited that those receiving SGLT2-I can significantly reduce inflammatory response and infarct size compared to those receiving other oral antidiabetic agents, and the use of SGLT2-I showed a lower risk of adverse cardiovascular outcomes (39, 40). The EMBODY study demonstrated that early SGLT2i administration might be effective in improving cardiac nerve activity without any adverse events (42). So far, the remaining five studies (EMPACT-MI, EMPRESS MI, DAPA-MI, NCT03658031, and NCT03591991) have not yet been published (9, 43). These studies did not explore the cellular-level mechanisms throughout their investigations, while our research endeavors to study the impact of SGLT2i on the structural aspects of the cardiac domain within the Asian population. To achieve this, we employ magnetic resonance imaging and blood work on its potential mechanisms underlying the favorable action on cardioprotection function. Additionally, such high-risk population with diabetes and AMI are commonly paid more attention on improvement in quality of life (14). A recent prospective study has provided compelling evidence suggesting the beneficial effect of empagliflozin on cognitive and physical impairment in frail older adults with T2DM and preserved ejection fraction (HFpEF) (44). This finding has sparked our interest in investigating whether the results are similar to those of a population with T2DM and AMI. KCCQ-OS is initially designed for patients with HF to evaluate symptom frequency, physical limitation, quality of life score, and social limitation (33). A recent cohort study included HFrEF patients exhibited that KCCQ-OS is more sensitive in health status over time than New York Heart Association (NYHA) class considering as a cornerstone for quantifying the health status of HF population (34). It is unknown whether KCCQ-OS is applicable to AMI population with high risks of HF. Moreover, we will also use EQ-5D to evaluate the quality of life in terms of five dimensions including mobility, self-care, activities, anxiety/depression, and pain/discomfort (35). Both full scores are ranging from 0 to 100, with higher scores reflecting better health status.

The underlying mechanisms of cardioprotection effects of SGLT2i are not completely understood, since only a few preclinical trials revealed that AMI mice treated with empagliflozin could improve LV remodeling by inhibiting cardiomyocyte apoptosis and altering myocardial substrate utilization (20, 21). Thus, we hope to explore the mechanistic benefits of SGLT2i in patients with AMI and provide evidence for early initiation following AMI. miRNAs, as noncoding RNAs, can regulate some posttranscriptional genes associated with the occurrence of AMI and are considered as early prediction markers with higher sensitivity than wildly acknowledged biomarkers (such as NT-pro BNP) (45). Additionally, a recent clinical study found that miR-29b levels were associated with changes of LVEDV (p < 0.05) measured by CMR over time after AMI (46). The latest research demonstrated that specific miRNAs (miR-126, miR-342-3p, miR-638, miR-21, and miR-92) were significantly regulated in T2DM and HFpEF patients and in response to empagliflozin (47). Current review suggested that four miRNAs (miR-29a, miR-29b, miR-150, and miR-30a-5p) may be prognostic markers in the patient’s clinical status associated with post-AMI LV dysfunction (48). Therefore, the involving panel of candidate miRNAs are measured to understand pathophysiological effects of SGLT2i and its correlation with CMR, as well as alterations in creatine kinase, TnI, or TnT level—diagnostic parameters indicative of AMI. The other exploratory mechanism is by changing FGF21 level. In recent clinical trials, FGF21 was proven to be an independent predictor of coronary heart disease in patients with T2DM and increased cardiovascular risks and was used as a novel biomarker to predict major adverse cardiovascular events (MACEs) in patients with STEMI after PCI (49–51). Our study is designed to test the hypothesis that treatment with SGLT2i changes FGF21 levels in patients with AMI.

The main strengths of this study are that we investigate the effects of SGLT2i on LV function using CMR technology in real-world scenario. Moreover, it explores the potential underlying mechanism that preserves ventricular function in these high-risk patients. Furthermore, the assessment of quality of life in AMI patients at high risk for HF on SGLT2i is conducted using KCCQ and EQ-5D.

However, it is important to acknowledge certain limitations of this study. This trial is a parallel group and single-center research that recruits patients with T2DM and severe AMI with complex conditions such as HF or CKD. Thus, whether these findings can speculate to other more uncomplicated patients needs to be further studied. To enhance the credibility of the results, the study employs univariate and multivariate analyses to migrate the possible influences.

